### Sample Size

As this study focuses on feasibility rather than achieving statistical significance, formal power calculations were not conducted prior to its initiation. Instead, the emphasis lies on assessing safety, feasibility, and generating preliminary data.

With no prior data on the use of this bone graft material in humans, the sample size was determined based on practical considerations, including resource availability, feasibility of recruitment within the study timeline, and ethical concerns regarding participant risk exposure. The aim was to enroll a sample size, allowing for meaningful observations and providing valuable preliminary insights into safety and efficacy.

Furthermore, following a common rule of thumb for pilot studies, which typically suggest around 30 participants, we decided on a sample size of 30 extractions, with 15 extraction sockets in each group. The number of sockets per patient varies based on individual clinical circumstances. This sample size was deemed appropriate for assessing safety, feasibility, and generating preliminary efficacy data.

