**Methods:**

This preliminary clinical trial will involve 30 fresh extraction sockets from individuals aged 18-35 years. The participants will be divided into 2 groups: one group will receive α-CSH graft material after tooth extraction for socket preservation, while the other group will not receive any graft material. Throughout the study, the participants will be closely monitored for safety measures, which will include clinical examinations, radiographic imaging, and blood tests. Radiographic imaging will be used extensively to assist the progress of bone formation.

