### Study Design

This prospective control clinical trial will be conducted at a single center and will involve 30 targeted extraction sockets after the removal of impacted mandibular third molars. This case is chosen as it represents a common scenario requiring extraction and often involving the removal of a significant amount of bone, making it an ideal model for studying human alveolar bone loss for socket preservation. The study aims to evaluate the efficacy of a high-purity α-CSH bioceramic (CaSO_4_·0.5H_2_O), synthesized from calcium sulfate dihydrate (CSD) without the use of chemical reagents, as a bone graft material in the alveolar bone loss case.

The 30 extraction sockets will be randomly assigned into 2 groups: 15 will receive α-CSH as a bone graft, while the other 15 will not receive any graft material. The main end point will be evaluated 6 months into the procedure. During follow-up visits, any adverse events or serious adverse events will be carefully documented, and clinical assessments will be conducted as specified in the “intervention section.” All patients will undergo regular monitoring through clinical examinations, radiographs, lab tests, and any additional necessary procedures. Ultimately, the study will publish a comprehensive report on the feasibility and potential efficacy of the α-CSH approach in promoting bone formation, regardless of the outcome.

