### Randomization and Blinding

The allocation of participants into the treatment and control groups will be determined through randomization. This process will be conducted using a secure computer system for central randomization. Each patient will be assigned a unique study code, and their data will be provided to the operators and research evaluators in a format that preserves patient confidentiality through coding. When evaluating the data, the radiologist and the statistician will be blinded to the treatment.

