### Statistical Analysis

Statistical analysis will be performed using SPSS 16.0 (IBM Corp). Student *t* test will be used to analyze the difference between groups and different follow-up points. The statistical significance level will be set at a *P* value of .05 or lower.

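### The protocol randomises sockets in one place and participants in another, lets a patient contribute more than one socket, and names a t test with no patient term, so the test's error rate depends on facts it leaves open

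*Protocol article*

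**What the plan says.** All references are to the Protocol article.

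- **Study Design**, unit is the socket: "The 30 extraction sockets will be randomly assigned into 2 groups: 15 will receive α-CSH as a bone graft", and the other 15 get no graft.
- **Randomization and Blinding**, unit is the person: "The allocation of participants into the treatment and control groups will be determined through randomization". The Abstract (Methods) agrees: "The participants will be divided into 2 groups".
- **Sample Size**: no power calculation was made. The number comes from a rule of thumb used in pilot work: "which typically suggest around 30 participants, we decided on a sample size of 30 extractions, with 15 extraction sockets in each group". The same paragraph adds: "The number of sockets per patient varies based on individual clinical circumstances".
- **Statistical Analysis**: the one method named is the Student t test, which "test will be used to analyze the difference between groups and different follow-up points", at a significance level of .05. Neither a patient term nor a paired form is mentioned.
- **Inclusion and Exclusion Criteria**: no limit of one socket per patient. No section says how two sockets of one patient are to be allocated.

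**The concern.** The two statements of the randomised unit agree only if each patient gives exactly one socket, and Sample Size says that this is not so. The tooth studied is the mandibular third molar, which a patient can have on both sides.

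Two sockets in one mouth share the patient's bone biology, hygiene and smoking habits, so their ridge-width changes are likely to be correlated. A t test on 15 and 15 sockets treats all 30 values as independent. Whether this matters, and in which direction, depends on how the sockets of one patient are allocated, which is the point on which the protocol conflicts.

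At stake are the calibration of the trial's only inferential comparison, and the precision that a later, larger trial would take from these data. The number of independent people is also at stake, because recruitment, withdrawal and systemic adverse events are counted per patient.

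**Working it through.** **Plan's own figure.** 15 + 15 = 30 sockets, which agrees. No effect size, standard deviation or power is given, so no formula can reproduce 30.

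**Patients behind 30 sockets.** With at most two mandibular third molars per patient (assumption), the range is 30/2 = 15 to 30/1 = 30 patients.

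**Inputs not in the protocol (assumed).** Within-patient correlation (ICC) 0.3, 0.5 or 0.7; k two-socket (bilateral) patients; two-sided test at 0.05; normal outcomes. Type I error was simulated with 40,000 to 100,000 trials per cell. Repeat runs differ by about 0.2 percentage points.

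**(a) Patients randomised, both sockets in the same arm.** Each arm has k bilateral patients and 15 − 2k patients with one socket. With m sockets per patient:

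design effect = 1 + (Σm²/Σm − 1) × ICC = 1 + (2k/15) × ICC

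The true standard error is the naive one times the square root of the design effect.

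- k = 1, ICC 0.3: 1 + 0.133 × 0.3 = 1.04, so SE × 1.02. ICC 0.7: 1.09, so SE × 1.05.
- k = 7, ICC 0.3: 1 + 0.933 × 0.3 = 1.28, so SE × 1.13 and 15/1.28 = 11.7 effective sockets per arm. ICC 0.7: 1.653, so SE × 1.29 and 15/1.653 = 9.1 effective sockets.

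Type I error of the ordinary t test at a nominal 5%:

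| Bilateral patients per arm | ICC 0.3 | ICC 0.5 | ICC 0.7 |
|---|---|---|---|
| 1 | 5.6% | 5.7% | 6.1% |
| 2 | 5.9% | 6.4% | 7.2% |
| 3 | 6.4% | 7.5% | 8.4% |
| 5 | 7.5% | 9.2% | 11.2% |
| 7 | 8.5% | 11.2% | 13.5% |

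A repeat run gave 5.6% to 6.0% for the first row and 8.7% to 13.7% for the last.

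**(b) Sockets randomised 15:15 without restriction** (the literal reading of Study Design). Once one socket of a patient is placed, 14 of the 29 remaining places are in the same arm and 15 in the other. The two sockets therefore fall together or apart about equally often, and the opposite effects on the standard error balance over the randomisation. Simulated type I error was 4.8% to 5.2% over the ICC range, including the extreme of 15 bilateral patients. The loss is efficiency: where a patient's sockets fall in opposite arms, the within-patient contrast is not used.

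**(c) Two sockets forced into opposite arms** (not stated in the protocol; shown as a bound). With 15 such patients, the true variance of the difference is 1 − ICC times the assumed one: 0.7, 0.5 and 0.3. Type I error of the unpaired test is about 2.0%, 0.8% and 0.1%. For an assumed effect of 0.8 SD, power is about 57%, 59% and 60% unpaired, against 68%, 82% and 96% paired.

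**(d) One socket per patient, or ICC = 0.** The ordinary t test holds its 5%.

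**The case against.** The strongest objection is that a reader might infer that the standard errors and P values are bound to be wrong. The documents do not support that. Under the literal wording of Study Design, case (b), the average error rate is right. Under patient randomisation with few bilateral patients it is only slightly high. The protocol does not say how many patients are bilateral. This objection stands, and it makes the size of the problem conditional.

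A reader might also take socket randomisation to mean a split-mouth design. No section says that a patient's sockets must go to opposite arms, so the figures in (c) are a bound and do not describe this trial.

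Nor does the protocol promise 30 participants. It says openly that the 30 are extractions; the fault is only that a rule stated in participants is used to justify them.

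Two further objections stand in part. The article is condensed, and does not say whether the t test is paired or how bilateral patients are handled; an analysis plan may do so. That the test takes the sockets as independent is therefore an inference, though a natural one from groups counted as 15 and 15 sockets. An unseen plan would not remove the conflict between the article's own statements of the unit. The trial also puts feasibility ahead of significance, which lowers the consequence. It does not remove it, because a .05 threshold is set and preliminary efficacy data are promised.

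**Conclusion.** The concern holds in conditional form. The conflict over the randomised unit, together with a varying number of sockets per patient, is plain on the page and needs no assumption. The statistical consequence does need assumptions. For ICC 0.3 to 0.7, type I error is about 6% to 14% if patients are randomised (one to seven bilateral patients per arm). It is near 5% on average, with lost efficiency, if sockets are randomised freely. It is below 5%, with lost power, only under a split-mouth rule that the protocol does not contain. If every patient gives one socket, nothing is wrong with the test on this account. The 30 sockets represent somewhere between 15 and 30 people, so the participant rule of thumb does not support the number. Severity is moderate, because this is a feasibility trial without a power claim.

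**What to change.** 1. State the unit that the central system actually randomises, and bring the Abstract, Study Design, and Randomization and Blinding into line with it. Say how two sockets of one patient are allocated.
2. Analyse the between-group difference in ridge-width change with a model that has a random patient effect and small-sample degrees of freedom (Kenward-Roger or Satterthwaite). If the 3- and 6-month values are modelled together, add a socket-within-patient term. Simpler choices would also do: one mean value per patient if patients are randomised, or a paired analysis if the design proves to be fully split-mouth.
3. Report the number of patients and of bilateral patients beside the 30 sockets, and drop the participant rule as the justification for 30 sockets.

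The cost is analysis and wording only, since each patient already has a study code. The stated number of independent units becomes less favourable, and software other than the named SPSS 16.0 may be needed for the small-sample correction.

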### Randomization and Blinding

The allocation of participants into the treatment and control groups will be determined through randomization. This process will be conducted using a secure computer system for central randomization. Each patient will be assigned a unique study code, and their data will be provided to the operators and research evaluators in a format that preserves patient confidentiality through coding. When evaluating the data, the radiologist and the statistician will be blinded to the treatment.

### Data Collection and Access

The study team will receive detailed guidelines and responsibilities. The medical professionals within the research team will collect the required information as outlined in Table 1. Training sessions will be conducted for the entire research team to ensure consistent data collection at each study visit. The clinical assessors and investigators will receive the data in a format that maintains patient confidentiality through coding. The participants will be monitored for a maximum duration of 6 months. The data manager will prioritize the confidentiality and security of the participant's data.

**Table 1 table1:** Assessment of clinical trial.

	Consent form	Clinical photograph	Panoramic	CBCT^a^	Blood test	Probing	Physical examination
Preoperatively	✓	—^b^	✓	✓	✓	✓	✓
Operative day	—	✓	—	—	—	—	✓
Postop day 7	—	✓	—	—	—	—	✓
Postop day 14	—	✓	—	—	—	—	✓
Postop day 90	—	✓	✓	✓	—	✓	✓
Postop day 180	—	✓	✓	✓	—	✓	✓

^a^CBCT: cone-beam computed tomography.

^b^Not applicable.

### Outcomes

#### Feasibility Assessment

The assessment of α-CSH safety in the present context will focus on the occurrence of serious adverse events. To deem α-CSH as safe, it should not result in a higher frequency of adverse events compared to standard treatment (without socket preservation). Additionally, any adverse events that do arise should be manageable through established noninvasive procedures such as analgesics and antibiotics. The evaluation of safety will play a crucial role in determining the suitability and viability of α-CSH in the study.

Feasibility evaluation was conducted using intraoral clinical examination and photographs to assess potential complications such as inflammation, infection, dehiscence, and graft loss. Graft loss will be evaluated in the early postoperative period, within the first week, and late postoperative period. The progress of wound healing at the surgical sites will be assessed with the Landry wound healing index [23]. This index considers factors such as the color of the soft tissue (pink or red), presence of suppuration, amount of bleeding, presence of granulation tissue, and exposure of connective tissue. Based on these criteria, the healing process was categorized into 5 distinct categories, namely very poor, poor, good, very good, and excellent [23]. Patients were also asked about any pain in the surgical site or adjacent areas during the follow-up period.

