### Adverse Event and Severe Adverse Event Assessment

Adverse events encountered during the study will be classified as serious or nonserious based on severity using the classification system established by the World Health Organization [22]. Participants who experience any adverse events will receive comprehensive medical care to address their needs. Any changes in the participant’s health status that occur between

the screening examination and the initial administration of α-CSH or associated procedures will be documented in their medical records. In the event of a severe adverse event, the principal investigator will be promptly notified within 24 hours of its occurrence. If the severe adverse event is determined to be associated with severe toxicity or infection at the transplant site, the experiment will be immediately halted to ensure participant safety.

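### The condition for deeming α-CSH safe compares adverse-event frequencies in 15 v 15 sockets with no margin or interval, so passing or failing it says little about safety

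*Protocol article*

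**What the plan says.** Feasibility Assessment opens with the stated focus: "The assessment of α-CSH safety in the present context will focus on the occurrence of serious adverse events". The next sentence sets the condition for calling the material safe, and it concerns adverse events in general: "it should not result in a higher frequency of adverse events compared to standard treatment (without socket preservation". A further condition follows: "any adverse events that do arise should be manageable through established noninvasive procedures such as analgesics and antibiotics". No margin, interval or counting unit is attached to the frequency comparison.

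The next paragraph of that section uses examination and photographs to "assess potential complications such as inflammation, infection, dehiscence, and graft loss". Interventions states that control sockets receive no graft material.

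Study Design fixes the numbers: "15 will receive α-CSH as a bone graft, while the other 15 will not receive any graft material". Sample Size says that no power calculation was made, that 30 extractions follow a rule of thumb for pilot studies, and that the number of sockets per patient varies.

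**The concern.** The protocol calls the safety evaluation crucial to judging whether the material is suitable and viable, and describes the trial as the first in humans. A condition that asks only whether one frequency exceeds another takes no account of chance. With 15 sockets per arm, one or two events can decide it. A material no worse than control can fail, and one with a doubled event rate can pass.

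Two ambiguities add to this. The stated focus is serious events but the condition covers all adverse events, and the rule behaves differently for rare and common events. Graft loss is also listed among the complications. If it enters the count, the comparison tilts against α-CSH, because an ungrafted socket has no graft to lose.

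**Working it through.** **Inputs.** From the protocol: n = 15 sockets per arm (Study Design, Sample Size); pass if the α-CSH frequency is not above control (Feasibility Assessment); no graft in controls (Interventions). Assumed: all event rates, since the protocol gives none; independent sockets; at most one counted event per socket. The protocol states no error rate for this rule, so there is no figure of its own to reproduce.

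**Formula.** Let X_T and X_C be independent Binomial(15, p_T) and Binomial(15, p_C). The frequency condition is passed when X_T ≤ X_C. With equal rates, P(fail) = (1 − P(tie))/2.

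**Equal true rates.**

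| Rate in both arms | P(tie) | P(fail) |
|---|---|---|
| 1% | 0.757 | 12.2% |
| 2% | 0.598 | 20.1% |
| 5% | 0.368 | 31.6% |
| 10% | 0.250 | 37.5% |
| 20% | 0.182 | 40.9% |
| 30% | 0.158 | 42.1% |

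Example at 20%: (1 − 0.182)/2 = 0.409.

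**True rate doubled by α-CSH.**

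| α-CSH v control | P(pass frequency condition) |
|---|---|
| 4% v 2% | 63.4% |
| 10% v 5% | 44.1% |
| 20% v 10% | 30.2% |
| 30% v 15% | 21.7% |

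The second condition can only remove passes, so these are upper bounds on the chance of a safe verdict.

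**Graft loss counted as an adverse event.** With background rate p in both arms and graft-loss rate g in the α-CSH arm only, p_T = 1 − (1 − p)(1 − g). At p = 20%:

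| Assumed g | p_T | P(fail) |
|---|---|---|
| 0 | 0.200 | 40.9% |
| 2% | 1 − 0.8 × 0.98 = 0.216 | 45.3% |
| 5% | 1 − 0.8 × 0.95 = 0.240 | 51.8% |
| 10% | 1 − 0.8 × 0.90 = 0.280 | 61.9% |

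**Is it only the sample size?** No. With equal rates of 20%, P(fail) is 46.5% at 100 per arm and 48.4% at 500. As ties become rare, a zero-margin comparison of observed frequencies tends to 50% failure for an equal material.

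**What 15 per arm can support.** The approximate 95% half-width for a risk difference is 1.96 × √(2p(1 − p)/15): 21, 29 and 33 percentage points at p = 10%, 20% and 30%. With no serious events among n independent patients, the one-sided 95% upper limit is 1 − 0.05^(1/n): 18.1% for n = 15 and 25.9% for n = 10.

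**The case against.** The strongest reply is that this is a pilot study. Sample Size disclaims statistical significance and asks only for preliminary data. Participants are protected by the care, 24-hour notification and halting provisions, not by an end-of-study label. The margin, interval and counting unit could sit in an analysis plan that is not shown. That excuses the absent power calculation, and it means the figures above apply to one reading, the comparison of observed frequencies. It does not excuse printing a condition for the word safe that, on this plain reading, cannot bear that weight.

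A reader might infer more than the documents support:

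- **That the rule is a coin toss.** This is roughly so only when true rates are equal and about 10% or more. At equal rates of 1–2% failure is 12–20%, and under large harm (30% v 10%) the condition is passed only 11.7% of the time.
- **That α-CSH is declared safe whenever its frequency is not higher.** The frequency condition is necessary but not sufficient, because noninvasive manageability is also required.
- **That graft loss will be counted.** It is called a complication in a feasibility paragraph, and is neither named as an adverse event nor excluded. The tilt is a possibility, and its size depends on an assumed rate.
- **That the serious-event classification is wrong.** The protocol says events "will be classified as serious or nonserious based on severity", which is loose wording, but it refers to a World Health Organization system that is not at hand, so the classification itself cannot be judged here.
- **That the verdict lacks laboratory data it relies on.** Feasibility Assessment does not rest the verdict on laboratory tests. The mismatch over blood tests is a separate scheduling inconsistency.

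It is also fair to say that 15 sockets need not be 15 people, so the binomial figures are themselves approximate.

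**Conclusion.** The point stands in a limited form. The frequency condition has no margin or interval, and it moves from serious events to all adverse events. On the observed-frequency reading it often fails an equal material once events are reasonably common, and often passes a doubled rate when events are rare. If serious events alone were meant, it would mostly pass, but it would also pass 63% of the time with a doubling from 2% to 4%, so it would still tell little. Counting graft loss would make failure more likely, by an amount that depends on its rate.

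All of these figures rest on assumed event rates and independent sockets. Several sockets per patient would break that independence, and an upper limit calculated on patients would then be wider.

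**What to change.** Replace the pass/fail frequency condition with estimation:

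1. Define one composite of complications that both arms can have (infection, dehiscence or inflammation through day 180). Report it by arm with the risk difference and an exact or Newcombe 95% CI. Use patients as the unit, or a method that allows for several sockets per patient.
2. Report serious adverse events by arm with an exact upper limit. State that 0/15 independent patients excludes only rates above about 18%, and that the limit is wider with fewer patients (about 26% with 10).
3. Report graft loss as a single-arm feasibility rate, outside the between-arm comparison.
4. State whether the safety statement rests on serious or on all adverse events.
5. Word the conclusion as *no safety signal at this sample size*, not as *safe*.

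These are changes to wording and analysis and need no new data. The cost is a weaker safety claim.

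Separately, reconcile the laboratory statements. The Abstract lists blood tests among safety measures during the study, and Study Design says "All patients will undergo regular monitoring through clinical examinations, radiographs, lab tests, and any additional necessary procedures", but Table 1 schedules a blood test only before surgery. The cost of that correction depends on how the sponsor resolves it.
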